### Randomization, allocation concealment, and blinding

2.8

Participants will be divided into two groups: the acupuncture group (receiving acupuncture treatment) and the sham acupuncture group (receiving pseudo-acupuncture treatment). The allocation ratio is set to 1:1 (*n* = 64), with randomization executed using a random group number generator in SPSS software (IBM, Armonk, NY, USA). Random numbers will be placed in opaque envelopes, which will be sealed and labeled with corresponding serial numbers to ensure confidentiality. The envelopes will be opened sequentially, and participants will be assigned to their respective treatment groups.

While patients in this trial will be blinded, it is nearly impossible to blind the practitioners and operators since they must know which acupuncture devices to use. They are prohibited from discussing the acupuncture devices or the study’s purpose with participants. Operators and assessors will be kept separate, and data analysis will be performed by an independent team. Outcome assessors and statisticians will be blinded to the treatment distribution.

To evaluate the success of blinding, patients will complete a blinding validation questionnaire (BTQ) immediately after their treatment. The BTQ consists of five questions. Blinding is considered successful if a participant completes all five questions without hesitation, reports no unusual sensations, and does not deny receiving acupuncture. Conversely, blinding is considered unsuccessful if participants identify any unusual elements of the questionnaire or deny receiving acupuncture. Otherwise, it is deemed successful.

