### Acupuncture operation

2.12

During the operation, participants will be instructed to wear eye masks and perform the head stitch while seated. First, the location of the scalp acupoint will be identified, and the tip of the needle will be inserted diagonally below the subcutaneous fascia along the acupoint area from top to bottom. The needle should be positioned at an angle of 15° to 30° relative to the scalp, with the tip from the top down into the subcutaneous fascia and then advanced 0.5 to1.0 cun along the scalp acupoint line.

Participants will be then be instructed to perform body acupuncture procedures in a supine position. Once their breathing is stable and their bodies are fully relaxed, the following steps will be performed: The needle will be inserted straight into the acupoints LI4, SP6, and LR3. For LI4 and SP6, the insertion depth should range from 0.5 to 0.8 cun, whereas for LR3, the depth should range from 0.3 to 0.5 cun. The needles should be inserted at an angle of 15° to 30° from the skin surface to ensure proper stimulation.

Additionally, a straight insertion will be performed into LI11, CV12, ST25, and CV6. The insertion depth for LI11 and CV12 should be between 1.0 and 2.5 cun, while for ST25 and CV6, it should be between 0.8 and 1.0 cun. The needles should be inserted perpendicularly to the skin at a 90° angle.

Finally, the needle will be inserted from the outer side of the calf toward GB34 and ST36 at a 90° angle, either straight or obliquely, to a depth of 1.5 cun. The insertion should be done carefully to avoid discomfort. After insertion, the needles at LI11, CV12, ST25, CV6, ST36, and GB34 can be lifted and twisted gently to enhance stimulation, generating a local swelling sensation that indicates the achievement of deqi. In Traditional Chinese Medicine (TCM), deqi is a key concept in acupuncture and moxibustion, signifying the achievement of an optimal therapeutic state during the course of treatment (MacPherson and Asghar, 2006; Zhou et al., 2011).

During the procedure, sterile disposable filament needles, measuring between 25 and 40 mm in length and 0.25 mm in diameter will be utilized, along with appropriate fixation tools (details are presented in Figure 3). The needles are manufactured by Suzhou Huatuo Medical Equipment Company in China to ensure quality and safety.

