### Sham acupuncture operation

2.13

The acupoints utilized in the sham acupuncture group will mirror those of the acupuncture treatment group. The sham acupuncture group will utilize non-penetrating retractable blunt needles and fixation tools that do not penetrate, which also measure between 25 and 25 mm in length and 0.25 mm in diameter, sourced from the same manufacturer (details are presented in Figure 3). Patients in this group will wear the same eye masks as those in the acupuncture group. The sham procedure will employ the same number of needles and last the same duration as the acupuncture procedure. Acupuncture points on the head will be secured with tape, while those on the body will be stabilized using the device depicted in Figure 3. All operational details will be meticulously documented.

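### The blinding-success rule contradicts itself and does not measure blinding in the acupuncture arm

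*Protocol article*

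**What the plan says.** Section 2.8 (Randomization, allocation concealment, and blinding) relies on patient blinding and concedes that those who needle cannot be blinded: "While patients in this trial will be blinded, it is nearly impossible to blind the practitioners and operators". It describes one check on patient blinding: "patients will complete a blinding validation questionnaire (BTQ) immediately after their treatment". The questionnaire has five items, which the article does not reproduce. Three sentences then score it:

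1. Success: "Blinding is considered successful if a participant completes all five questions without hesitation, reports no unusual sensations, and does not deny receiving acupuncture".
2. Failure: "blinding is considered unsuccessful if participants identify any unusual elements of the questionnaire or deny receiving acupuncture".
3. Everything else: "Otherwise, it is deemed successful".

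The rule is the same for both arms and does not refer to the treatment received. The section does not say whether the result is to be pooled or shown by arm. It gives the allocation as "The allocation ratio is set to 1:1 (*n* = 64", which is 32 per arm.

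Two other sections give context. In section 2.12, real needles at several body points may be manipulated, "generating a local swelling sensation that indicates the achievement of deqi". In section 2.13, "The sham acupuncture group will utilize non-penetrating retractable blunt needles and fixation tools that do not penetrate".

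**The concern.** Blinding is intact when patients cannot tell which arm they are in. A check on it has to set what each patient believes against what that patient received. This rule asks instead whether the patient accepts having had acupuncture, which is the right answer in one arm and the wrong answer in the other. The same score therefore has opposite meanings in the two arms.

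The three sentences also disagree about which answers count as successes, so two people scoring the same questionnaire could reach different results.

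At stake is how the trial's blinding result is read. The UPDRS III, balance and gait outcomes depend on what the patient does during the test, and expectation can affect that even when the assessor is blinded. A reader will look to this questionnaire for reassurance, and a high success rate under the stated rule would not provide it.

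**Working it through.** **Step 1: the three sentences side by side.** The plan states no blinding figure, so there is none to reproduce. Applying each sentence to each type of answer gives:

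| Answer | Sentence 1 (success) | Sentence 2 (failure) | Sentence 3 (default) | Final score |
|---|---|---|---|---|
| Denies acupuncture | not met | listed | – | failure |
| Identifies something unusual in the questionnaire | – | listed | – | failure |
| Hesitates | not met | not listed | applies | success |
| Leaves items incomplete | not met | not listed | applies | success |
| Reports an unusual sensation | not met | not listed | applies | success |

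Only the non-denial condition of sentence 1 keeps its effect. The conditions on complete, unhesitating answers and on sensations are cancelled by sentence 3. Read literally, the other failure criterion concerns the questionnaire rather than the treatment.

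**Step 2: the rule against actual allocation.** Inputs: 64 patients at 1:1, so 64/2 = 32 per arm (section 2.8). The answer patterns are assumptions, not trial data. A guess of sham is treated as a denial, and an unsure patient does not deny.

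- Rule success in an arm = (patients not denying acupuncture)/32.
- Bang's index in an arm = (correct guesses − incorrect guesses)/32. Zero is chance, +1 is all correct and −1 is all wrong.

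| Assumed pattern | Rule, acupuncture | Rule, sham | Rule, pooled | Bang, acupuncture | Bang, sham |
|---|---|---|---|---|---|
| All guess correctly | 32/32 = 100% | 0/32 = 0% | 32/64 = 50% | +1.00 | +1.00 |
| All guess at random (16/16) | 16/32 = 50% | 16/32 = 50% | 32/64 = 50% | 0 | 0 |
| All guess wrongly | 0/32 = 0% | 32/32 = 100% | 32/64 = 50% | −1.00 | −1.00 |
| Acupuncture arm certain, sham arm all unsure | 32/32 = 100% | 32/32 = 100% | 64/64 = 100% | +1.00 | 0 |
| All believe they had acupuncture | 32/32 = 100% | 32/32 = 100% | 64/64 = 100% | +1.00 | −1.00 |
| All unsure | 32/32 = 100% | 32/32 = 100% | 64/64 = 100% | 0 | 0 |

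**Step 3: why the pooled rate stays at 50%.** With no unsure answers, the acupuncture-arm rate is (1 + B_acu)/2 and the sham-arm rate is (1 − B_sham)/2, where B is Bang's index. With equal arms the pooled rate is their average:

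pooled = 1/2 + (B_acu − B_sham)/4.

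When the two indices are equal the second term is zero, so unblinding of the same degree in both arms leaves the pooled rate at 50%.

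**Step 4: by arm.** Over the first three rows the sham-arm rate moves as it should: 0% under full unblinding, 50% at chance, 100% when all are wrong. The acupuncture-arm rate moves the opposite way: 100%, 50%, 0%. The last three rows show that 100% success in both arms fits three quite different states of belief.

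**The case against.** The strongest reply is that the rule does detect what matters most in a sham-controlled trial. A sham patient who recognises the sham and says so is scored a failure. That is correct. A reader might infer that the rule cannot detect unblinding at all, and the text does not support this: in the first row of the table the sham-arm rate falls to 0%.

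A reader might also picture 100% success while half the sham arm suspects sham. That needs suspicion which the questionnaire fails to draw out, and its items are not shown. If 16 of 32 sham patients said they had sham, they would fail and the pooled rate would be (32 + 16)/64 = 75%. The rule does not count undeclared suspicion, but the documents give no basis for its size.

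A third inference is that the sensation condition is biased by arm, because a needling sensation is sought only with real needles. Once the default sentence applies, that condition no longer affects the score. That patients would call an expected sensation unusual is also an assumption.

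Nor does it follow that the trial could not separate a specific effect from expectation. The questionnaire measures blinding and does not create it. The sham uses the same points, number of needles, duration and eye masks; assessors and statisticians are blinded; and no efficacy analysis in section 2.17 uses the questionnaire.

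Finally, this is a condensed article. The five items may include a treatment guess, no pooled rate is announced, and tabulation by arm may be left to a fuller document. Those omissions are not the point here. The scoring rule is printed in full, it uses no guess, and its faults remain if results are shown by arm.

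**Conclusion.** The point holds in a limited form. The scoring rule contradicts itself: the default sentence turns hesitant, incomplete and unusual-sensation answers into successes. It also does not measure blinding in the acupuncture arm, where correct awareness counts as success and a mistaken denial as failure. In the sham arm it detects explicit denial but misses unsure patients and undeclared suspicion.

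The size is illustrative. It rests on 32 per arm, assumed answer patterns, a sham guess counted as a denial, and a pooled rate that the article does not itself specify. Under those assumptions the pooled rate is 50% at full unblinding, at chance and when all are wrong. That the acupuncture-arm score runs the wrong way does not depend on pooling.

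The consequence is a blinding result that could mislead and should be corrected. The primary efficacy comparison is not affected.

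**What to change.** Delete the default sentence and replace the pass/fail rule. Record one guess (real, sham, do not know) from every patient at the end of treatment, before the week-4 UPDRS III. Tabulate the guesses by arm against actual allocation, and report Bang's blinding index with a 95% CI for each arm. Deleting the default sentence alone is not enough, because the rule would still ignore allocation and the sensation condition would come back into force.

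Any summary of the UPDRS III by guess should be labelled descriptive. The guess is made after randomization and may reflect perceived benefit, so such a summary cannot cleanly separate expectation from effect. The same caution applies to reading the index itself.

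The cost is one questionnaire item, if the five existing items do not already contain it, and one table. Sample size and the primary test stay as they are.

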### Sample size estimation

2.9

The sample size was determined based on the Unified Parkinson’s Disease Rating Scale (UPDRS) III motor assessment. A previous study (Jang et al., 2020a) provided the sample size estimation. Two-sided two-sample *t-*tests with a significance level of 0.05 were employed to achieve 80% power. The analysis indicated a standard deviation of 1.54 and a mean difference of 1.15 between the two groups. Consequently, the G-Power (v3.1) sample size calculation indicated that each group will consist of 29 patients diagnosed with PIGD-subtype PD, satisfying the inclusion and exclusion criteria. However, to accommodate a 10% attrition rate, the sample size for each group was increased to 32 patients.

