### Data analysis methods

2.17

Patient demographics, clinical characteristics, and gait data will be analyzed using SPSS V27.0. Measurement data will be expressed as mean ± standard deviation (mean ± SD) if they follow a normal distribution, while count data will be described using frequency and constituent ratio if they do not. For non-normally distributed data, the difference between the lower and upper quartiles (P25, P75) will be reported. Wilcoxon rank sum and Mann -Whitney U tests will be used for comparisons within and between groups. The chi-square test will be employed to analyze count data. Based on the normality of the data, either Pearson or Spearman correlation will be performed to analyze the correlations. This study will be deemed statistically significant at *p* < 0.05.

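### Section 2.9's 80% power is narrowly missed after 10% attrition, rests on a t-test that section 2.17 does not name for UPDRS III, and uses a difference and SD whose score type and visit are not stated

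*Protocol article*

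**What the plan says.** Protocol article, section 2.9 (Sample size estimation): "The sample size was determined based on the Unified Parkinson’s Disease Rating Scale (UPDRS) III motor assessment". A cited previous study "provided the sample size estimation". The method is a "Two-sided two-sample" t-test, and these "tests with a significance level of 0.05 were employed to achieve 80% power". For the inputs, "The analysis indicated a standard deviation of 1.54 and a mean difference of 1.15 between the two groups". The section reports 29 per arm from G-Power and adds that "to accommodate a 10% attrition rate, the sample size for each group was increased to 32 patients". Section 2.8 confirms 1:1 allocation and 64 patients in total.

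Section 2.17 (Data analysis methods): "Wilcoxon rank sum and Mann -Whitney U tests will be used for comparisons within and between groups". This comes directly after a sentence on how non-normal data are summarised. The section names no t-test and no baseline-adjusted model for the clinical outcomes.

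Section 2.15.1 schedules UPDRS III before inclusion, at 4 weeks and after the 8-week follow-up. It does not single out one of these as the primary time point.

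**The concern.** Three features separate the stated 80% from the trial as planned.

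1. The attrition allowance is calculated the wrong way round, so the expected number of completers falls just below the plan's own 29.
2. The test used for sizing is not one that section 2.17 names for comparing the groups on UPDRS III.
3. The difference and SD are given as bare numbers. A reader cannot tell whether they describe the UPDRS III score at a visit or its change from baseline, or at which visit.

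The third feature carries the most weight. A change SD and a visit SD can differ a good deal, and power moves quickly with the SD. If the trial ends with a null result, the reader needs to know how likely it was to detect 1.15 points, and section 2.9 does not allow that to be judged.

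**Working it through.** **Inputs.** From section 2.9: difference 1.15, SD 1.54, two-sided alpha 0.05, power 80%, attrition 10%, 29 raised to 32 per arm. Standardised difference d = 1.15/1.54 = 0.7468.

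**Reproducing 29.**
- Normal approximation: n = 2 × [1.54 × (1.960 + 0.842)/1.15]² = 28.15, so 29 per arm. This matches the plan.
- Exact noncentral t, d = 0.7468: 79.8% at 29 and 81.2% at 30.
- Exact noncentral t, d rounded to 0.75: 80.1% at 29. This also matches.

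The 29 is therefore reproducible, and the gap at unrounded d is 0.2 points.

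**Attrition step.**
- As done: 29 × 1.1 = 31.9, so 32.
- As needed: 29/0.9 = 32.2, so 33.
- Expected completers from 32: 32 × 0.9 = 28.8 per arm.

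**Power by number analysed per arm.** The t-test column is exact noncentral t. The Mann-Whitney column uses the same formula with n multiplied by 3/π = 0.955, its efficiency under normal data.

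| Analysed per arm | t-test | Mann-Whitney, normal data |
|---|---|---|
| 28 | 78.4% | 76.4% |
| 28.8 | 79.5% | 77.6% |
| 29 | 79.8% | 77.9% |
| 32 (no loss) | 83.7% | 81.9% |

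Simulation with 40,000 replicates agrees for the rank test: 76.5% at 28, 77.7% at 29 and 81.8% at 32.

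**What 1.54 measures.** Suppose 1.54 is the SD of change, while the groups are compared on scores at a visit. With equal variances at baseline and follow-up and correlation r between them, visit SD = 1.54/√(2(1 − r)). The article gives no r, so the values below are assumptions. Power is for a t-test at 28.8 per arm and a difference of 1.15.

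| Assumed r | Visit SD | Power |
|---|---|---|
| 0.5 | 1.54 | 79.5% |
| 0.7 | 1.99 | 58% |
| 0.8 | 2.43 | 42% |

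**Adjusting for baseline** (28.8 per arm).
- If 1.54 is a visit SD and r = 0.5 (both assumed), the residual SD is 1.54 × √(1 − 0.25) = 1.334, and ANCOVA power is about 89.5%, against 79.5% unadjusted.
- If 1.54 is a change SD, the residual SD is [1.54/√(2(1 − r))] × √(1 − r²). This is 1.461 at r = 0.8 (about 83.5%) and 1.501 at r = 0.9 (about 81.5%), against 79.5% for analysing change. The gain remains but shrinks as r rises.

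**The case against.** A reader might infer that the trial is underpowered or that its sample size calculation is wrong. The document does not support that.

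- The 29 follows from a standard formula and from a rounded effect size.
- The attrition slip costs one patient per arm, or 0.2 of an expected completer and 0.3 points of power. The 10% is itself a guess with more uncertainty than that.
- If everyone is analysed, 32 per arm gives more than 80% by either test. The article does not fix a completers-only analysis, so the loss to 28.8 is conditional.

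The rank-test point is also conditional. The sentence in section 2.17 follows one on non-normal data and may apply only there. The 0.955 efficiency is for normal data; with skewed or heavy-tailed scores a rank test can gain power. It cannot be said that the planned test lowers power in every case. Still, section 2.17 offers no other between-group test for UPDRS III if the data are normal.

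On the SD, the article does tie it to UPDRS III and to a cited study, which may define the score type and visit. The correlations used above are assumed, and nothing in the document makes an SD above 1.54 more likely than 1.54 itself. It would be wrong to conclude that true power is 42% or 58%. What stands is that section 2.9 chose to report the calculation and left out what is needed to interpret it.

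**Conclusion.** The point holds as a modest correction together with a clarification. On the plan's own inputs, 32 per arm less 10% gives about 79.5% power by t-test. It gives about 77.6% by Mann-Whitney, provided that test is applied to UPDRS III and the data are close to normal. The t-test shortfalls are under one point and would not justify action alone.

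The more consequential gap is that 1.15 and 1.54 carry no score type or visit. Under one possible mismatch, a change SD used to size a comparison of visit scores, power could be well below 80%. How far below depends on a correlation that the article does not give. A baseline-adjusted analysis would more than recover the t-test shortfall in the cases worked above, using data the trial already collects.

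**What to change.** 1. Keep 64 patients. In section 2.9, restate the power as about 78 to 80% by t-test with 28 to 29 evaluable per arm (about 76 to 78% by the rank test under normal data), and correct the attrition step to division by 0.9.
2. State whether 1.15 and 1.54 are visit or change values of UPDRS III, and at which visit.
3. In section 2.17, make the primary between-group analysis of UPDRS III an ANCOVA adjusted for baseline UPDRS III, and have section 2.9 refer to that analysis.
4. Optionally, add a short table of power over a range of assumed SDs.

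The cost is revised text in sections 2.9 and 2.17 and a slightly less favourable power statement for the unadjusted tests. No extra patients, visits or assessments are needed.

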### Intervention

2.10

Patients will receive standard medical treatment as outlined in the Parkinson’s Treatment guidelines (Pringsheim et al., 2021). This study includes both acupuncture and sham manipulation. The acupuncture group will receive an additional 30 min of acupuncture treatment. All acupuncture treatments will be performed by two senior physicians with over 5 years of clinical experience, administered three times weekly for 4 weeks.

### Acupuncture points

2.11

The acupuncture points selected include the upper 1/5 anterior oblique line of the vertex-temporal (MS6), the upper 1/5 posterior oblique line of the vertex-temporal (MS7), and the lower-lateral line of the occiput (MS14), according to the proposed standard international acupuncture nomenclature proposed by the WHO scientific group in 2020 (Wise and Lorenc, 2023). Additional acupuncture points include Hegu (LI4), Quchi (LI11), Taichong (LR3), Yanglingquan (GB34), Zusanli (ST36), Sanyinjiao (SP6), Zhongwan (CV12), Tianshu (ST25), and Qihai (CV6), following the standards set by the standards of The People’s Republic of China, GB/T12346-2006, 2006. Details of the selected acupoints are presented in Table 2 and Figure 2.

**Table 2 tab2:** Locations of scalp acupuncture lines and acupoints.

Points	Location
Anterior oblique line of vertex-temporal (MS6)	Located on the side of the top of the head, the line 1 cun anterior to Qianshenchong (one of the four acupuncture points collectively designated as Ex-HN1) obliquely to Xuanli (GB6).
Posterior oblique line of vertex-temporal (MS7)	Located on the side of the top of the head, 1 cun after the anterior oblique line of the parietal and temporal, and parallel to it, that is, the line from Baihui (GV20) obliquely to Qubin (GB7).
Lower-lateral line of the occiput (MS14)	Located in the occipital region, a line 2 cun long from Yuzhen (BL9) straight down.
Hegu (LI4)	Located on the back of the hand, between the first and second metacarpals, at the midpoint of the second metacarpal.
Taichong (LR3)	Located on the dorsum of the foot, between the 1st and 2nd metatarsal bones, in the anterior depression at the junction of the metatarsal base, or where the pulse can be felt.
Quchi (LI11)	Located at the elbow, specifically at the midpoint between the Qiuze (PC3) and the external epicondyle of the humerus.
Yanglingquan (GB34)	Located on the lateral side of the lower leg, in the depression near the anterior border of the fibula.
Zusanli (ST36)	Located on the lower leg, approximately 3 cun below ST 35 and one finger-width lateral to the anterior border of the tibia.
Sanyinjiao (SP6)	Located on the inner aspect of the lower leg, about 3 cun above the prominent bone on the inner ankle
Zhongwan (CV12)	Located on the midline of the abdomen, directly above the navel, approximately 4 cun below the sternal xiphoid process.
Tianshu (ST25)	Located on the midline of the abdomen, 2 cun lateral to the navel on both sides.
Qihai (CV6)	Located on the midline of the abdomen, approximately one and a half finger-widths below the navel.

